### Rescue therapy

In all three groups, clinicians can add or titrate diabetes medicine until week 24 if HbA1c ≥ 86 mmol/mol (10%) or symptoms of hyperglycemia or hypoglycemia develop. After week 24, diabetes medication can be changed if HbA1c ≥ 69 mmol/mol (8.5%) or symptoms of hyperglycemia or hypoglycemia develop. Additionally, in group C, clinicians may change the medication if frequent hypoglycemia (< 3.89 mmol/L (70 mg/dL), > 3% of total time of a day) or frequent hyperglycemia (> 9.99 mmol/L (180 mg/dL), > 30% of total time of a day) is reported on the CGMS.

### Discontinuation of subjects

Subjects may stop the intervention and be excluded if any of the following safety issues occur: 1) hyperosmolar hyperglycemic state (HHS) or 2) complicated systemic diseases that may have a significant impact on the clinical trial. Subjects also can be dropped if any of following situations occur: 1) the subject or legal representative requested to discontinue the study; 2) subjects who did not meet the selection criteria were included in the trial; 3) the subject does not or cannot comply with the visits and procedures specified in the trial plan; 4) follow-up loss of the subject; or 5) other problems that investigators consider to be inappropriate for continuing the trial.

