### Outcome variables

The primary outcome will be change in HbA1c from baseline to 6 months after intervention.

The main secondary outcome will be levels of HbA1c and fasting blood glucose at weeks 12, 24, 36, and 48. Other secondary outcomes include lipid profile (i.e., total cholesterol, high-density lipoprotein [HDL] cholesterol, triglycerides, and low-density lipoprotein [LDL] cholesterol) at weeks 24 and 48; the incidence of hypoglycemic events and adverse events at weeks 12, 24, 36, and 48; satisfaction evaluation according to the Diabetes Treatment Satisfaction Questionnaire (DTSQ) [9, 10] at weeks 12, 24, 36, and 48; mean body weight, BMI, and body fat mass for 1 week prior to weeks 12, 24, 36, and 48; mean number of steps, burned calories, and walking distance for 1 month prior to weeks 12, 24, 36, and 48; and mean calorie intake for 3 consecutive days prior to weeks 12, 24, 36, and 48. For experimental group C, secondary outcomes also include CGM metrics, specifically the values of mean glucose; coefficient of variation (CV); and percentages of time in range (TIR), time above range (TAR), and time below range (TBR) for 1 week prior to weeks 12, 24, 36, and 48, and the number of educational interventions by medical staff at weeks 12, 24, 36, and 48.

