### Sample size assumptions

Assuming a 0.3% difference in HbA1c values between the study groups (mean HbA1c 58 mmol/mol (7.44%) [standard deviation, 0.6%]) (effect size d = 0.50) according to previous studies, [7, 11] 78 subjects per group are required, with a two-sided alpha threshold of 0.05 and 80% power. Considering a dropout rate of 20%, the total number of patients required for this study is estimated to be 294 (98 patients per group) from the collective three hospitals.

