### Distribution and use of at-home measurement devices and the digital integrated healthcare platform

For subjects in experimental groups B and C, at-home measurement devices of a Bluetooth-enabled glucometer, scale with bioelectrical impedance analysis, sphygmomanometer, and watch-type pedometer will be provided. Subjects in group B will configure and apply these devices and the platform by themselves, while subjects in group C will be provided instruction regarding the configuration and use of the devices and the platform by medical staff during their hospital visit.

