#### Intervention

Subjects in group A will maintain routine diabetic care during the study period of 48 weeks. Subjects in group B will use a digital integrated healthcare platform by themselves to manage blood glucose during the study period, with no monitoring or intervention from medical staff.

Subjects in group C will be assisted by medical staff in installing the digital integrated healthcare platform when they visit their clinic and will apply the platform during the study period of 48 weeks. Investigators will continuously monitor all data collected from the digital integrated healthcare platform. Medical staff will motivate patients to maintain their self-care through ongoing personal monitoring and intervention. Participants of C group will be provided a copy of the food exchange table on the first day of the study. The daily calorie requirement for each participant is calculated based on the optimal body weight and normal activity level. Each subject in group C will receive a text message once a week via the digital healthcare platform. Clinical registered dietitians will send one of four types of nutritional intervention messages, which are categorized as warning, education, encouragement, or confirmation, based on blood glucose level, CGM metrics, body weight, blood pressure, activity level, and dietary records (Table 2). In addition, a nutritional education message will be sent every 4 weeks.

**Table 2 Tab2:** Contents of interventional text messages

Message type	Examples
Warning	• Warning for excessive calorie intake, extra snacks, high amount of sugar or alcohol consumption. • Lack of daily activity • Imbalance of food intake based on food group: for example, heavy intake of fruit or grains and insufficient intake of protein.
Education	• Card-type mini-educational messages according to the weekly meal pattern; for example, food exchange table, nutrition facts, calories of restaurant food, GI index, and the relationship between exercise and level of blood glucose.
Confirmation	• Verification of previous warning and educational messages • Feedback on daily practice • Instruction and assessment of weekly practice content
Encouragement	• Encouraging message to minimize the drop-out rate • Encouraging message for positive changes in diet or body weight, etc.

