## Discussion

In this study, the effect of a digital integrated healthcare platform will be investigated in patients with type 2 diabetes who have HbA1c 53–69 mmol/mol (7.0–8.5%) and body mass index (BMI) ≥ 23 mg/m^2^. We plan to apply a digital integrated healthcare platform using an artificial intelligence (AI)-based dietary management solution and a continuous glucose monitoring system (CGMS), and medical staff will continuously monitor the collected healthcare data and send regular educational messages via the platform to encourage efficient self-management of diabetes.

Previously, the efficacy of several smartphone apps for diabetes management was demonstrated via randomized controlled trial [5, 6]. However, even if the efficacy of apps has been demonstrated in clinical trials, the effect may decrease if the patient does not actively use the apps. In 2016, Payal Agarwal et al. [12] investigated the impact of “Bluestar,” an application developed for self-management of diabetes and approved by the Food and Drug Administration, among different clinical sites and health systems. They conducted a pragmatic, multicenter, randomized trial in three recruitment sites. They reported low usage of the app among participants, with a mean number of log-in days of 42.4 (SD 52.1) over 26 weeks, with 46.4% (51/110) of the participants using the app for 10 days or less, and the results showed no difference in HbA1c between the intervention and control groups [12].

One of the strengths of the present study is the use of an AI-driven dietary solution for the record of dietary intake. The image-assisted dietary assessment was shown in previous studies to reduce underreporting of dietary intake compared with traditional methods [13]. The dietary program in this study is expected to be more convenient and effective in that it recognizes all foods by a single capture utilizing the AI solution. Also, for user-friendliness, participants can see their various healthcare data, such as glucose level, body weight, blood pressure, daily activity, and dietary data, on the digital integrated healthcare platform app by connecting Bluetooth-enabled at-home measurement devices including a glucometer, scale, sphygmomanometer, and watch-type pedometer.

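### The discontinuation rule ties stopping the intervention to exclusion and lets non-compliant randomised patients be dropped, which can leave arm-dependent, outcome-related gaps in week-24 HbA1c

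*Protocol article*

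**What the plan says.** The protocol article, under Discontinuation of subjects, has two lists. The first covers hyperosmolar hyperglycaemic state and serious systemic disease: "Subjects may stop the intervention and be excluded if any of the following safety issues occur". The second allows a subject to be dropped on request, on loss to follow-up, at the investigator's judgement, when "subjects who did not meet the selection criteria were included in the trial", or when "the subject does not or cannot comply with the visits and procedures specified in the trial plan". Neither list says whether exclusion or dropping refers to the intervention, to follow-up or to the analysis.

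Under Outcome variables: "The primary outcome will be change in HbA1c from baseline to 6 months after intervention". Table 1 schedules laboratory tests for all arms at weeks 12, 24, 36 and 48, each within 14 days either side, and at one early-termination visit. Nothing is scheduled after that visit.

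The procedures differ by arm. Under Intervention: "Subjects in group A will maintain routine diabetic care during the study period of 48 weeks". Under the section on at-home devices: "Subjects in group B will configure and apply these devices and the platform by themselves". Groups B and C also photograph meals, and group C adds a week of CGM before each follow-up visit.

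Under Sample size assumptions: "Considering a dropout rate of 20%, the total number of patients required for this study is estimated to be 294".

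**The concern.** Two separate acts are joined: ending use of the platform and ending observation of the patient. A patient in A has visits and tests to comply with. A patient in B or C has those plus the devices, the app and the diet records. The non-compliance ground therefore has more to act on in the experimental arms, and staff and patients know the allocation.

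Non-compliance is also plausibly linked to outcome. The Discussion itself warns that "the effect may decrease if the patient does not actively use the apps" and cites a trial in which 46.4% of participants used the app on 10 days or fewer and HbA1c did not differ between groups. If patients who do not take to the platform leave before week 24, those who remain in B and C are a selected group, and the comparison with A no longer rests on randomisation alone. An analysis plan can define who is analysed, but it cannot supply a week-24 HbA1c that was never drawn. Trial conduct decides that, and the protocol governs conduct.

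**Working it through.** **The plan's own figure.** Taking 78 per group as given, 78 / (1 − 0.20) = 97.5, so 98 per group and 3 × 98 = 294. This reproduces. The inflation restores the number of observations; it does nothing about which patients are missing.

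**Where the gap arises.** A patient dropped between the week-12 visit and the opening of the week-24 window has a week-12 HbA1c and perhaps an early-termination value, but no week-24 value. A patient dropped after the week-24 visit still contributes to the primary outcome, so only removals before that visit matter for it. Later ones affect the week-36 and week-48 secondary outcomes.

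**Formula.** In one arm let p be the share removed, and g the amount by which the HbA1c change is worse in removed than in retained patients. If the arm's overall mean is m and the retained mean is r, then m = (1 − p)r + p(r + g), so r = m − pg. The comparison of retained patients therefore favours the platform arm by

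bias = p(B or C) × g(B or C) − p(A) × g(A),

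which is [p(B or C) − p(A)] × g when g is the same in both arms.

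**Inputs.** From the protocol: target difference 0.3, SD 0.6, 98 randomised per arm, two-sided alpha 0.05. Assumed, because the protocol gives none: the removal shares and g.

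With a true effect of zero and n = 98 × (1 − p) in each arm, SE = 0.6 × √(1/n(A) + 1/n(B or C)), and the false-positive rate is 1 − Φ(1.96 − bias/SE) + Φ(−1.96 − bias/SE).

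| Removed in A | Removed in B or C | g | Bias | Share of 0.3 | False-positive rate |
|---|---|---|---|---|---|
| 20% | 20% | 0.3 or 0.6 | 0 | 0% | 0.050 |
| 10% | 20% | 0.3 | 0.03 | 10% | 0.062 |
| 10% | 20% | 0.6 | 0.06 | 20% | 0.099 |
| 10% | 30% | 0.3 | 0.06 | 20% | 0.095 |
| 10% | 30% | 0.6 | 0.12 | 40% | 0.237 |

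For the last row: (0.30 − 0.10) × 0.6 = 0.12; n = 88.2 and 68.6; SE = 0.0966; bias/SE = 1.24.

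The sign can reverse. With 20% removed in A, 10% in C and g = 0.3, the bias is (0.10 − 0.20) × 0.3 = −0.03, against the platform.

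**The case against.** The wording is permissive, and nowhere does it say that data are discarded or that a patient leaves the primary analysis. Analysis sets and missing-data methods commonly sit in an analysis plan, which is not shown, so their absence here is no fault. That stands. What remains is the loss of the measurement itself. The early-termination test and the week-12 HbA1c soften that loss but do not replace the week-24 value.

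Several stronger readings are tempting, and the protocol does not support them:

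- A reader might infer that the rule does remove poor outcomes from the platform arms and inflates the effect. The rules apply to all arms, and missed visits count in A too. No app-use threshold is set. Some of group C's text messages are meant to limit drop-out, so C could lose fewer patients than A. Direction is not established.
- A reader might take the Discussion to say that low use is the main reason earlier apps failed. It reports that several apps worked in randomised trials, says that the effect may fall without active use, and cites one trial with low use and no difference.
- Hyperosmolar state is an extreme glycaemic outcome, but no rate or arm difference is given. If it occurred mainly in A, excluding it would shrink the platform effect. Late-found ineligibility is a baseline matter and is not shown to differ by arm.
- One could apply the whole 20% dropout to B and C as outcome-related and treat all loss in A as unrelated: 0.20 × 0.3 to 0.5 = 0.06 to 0.10. That is a one-sided scenario, and the 20% is a general allowance that would also cover patient request and loss to follow-up.
- One could claim the power of all 98 per group rather than 78. That is a ceiling: patients will still withdraw consent or be lost.

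**Conclusion.** The concern holds as a risk that the protocol's own rule creates, not as a demonstrated bias. The rule joins stopping the intervention to exclusion and permits dropping for non-compliance with procedures that differ by arm, and the schedule provides no HbA1c after early termination. Together these can produce missing week-24 values that depend on arm and outcome.

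The illustrative size is 0.03–0.12 HbA1c points, or 10–40% of the 0.3 target, with a false-positive rate of about 0.06–0.24 in place of 0.05. These figures assume 10% removal in A against 20–30% in B or C, a gap of 0.3–0.6 points that is the same in both arms, and an analysis of retained patients only. Equal removal with an equal gap gives no bias, and greater loss in A would reverse the sign. The point warrants correction before patients are dropped, because values not collected cannot be recovered.

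**What to change.** In the section on discontinuation, separate stopping the intervention from leaving the study. State that neither stopping the intervention nor non-compliance ends the scheduled HbA1c measurements unless the patient withdraws consent. State also that neither removes a randomised patient from the primary comparison by allocated group. Keep the early-termination visit for those who do leave the study. A per-protocol analysis may be reported as a sensitivity analysis.

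The clinical grounds for stopping the intervention, and the clinician's freedom to apply them, are unchanged.

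The cost is mainly wording, because visits and HbA1c tests every 12 weeks are already scheduled in all three arms. Some effort will be needed to keep non-compliant patients attending. The estimated effect may be somewhat diluted, since it will include patients who stopped using the platform.

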## Discussion

In this study, the effect of a digital integrated healthcare platform will be investigated in patients with type 2 diabetes who have HbA1c 53–69 mmol/mol (7.0–8.5%) and body mass index (BMI) ≥ 23 mg/m^2^. We plan to apply a digital integrated healthcare platform using an artificial intelligence (AI)-based dietary management solution and a continuous glucose monitoring system (CGMS), and medical staff will continuously monitor the collected healthcare data and send regular educational messages via the platform to encourage efficient self-management of diabetes.

Previously, the efficacy of several smartphone apps for diabetes management was demonstrated via randomized controlled trial [5, 6]. However, even if the efficacy of apps has been demonstrated in clinical trials, the effect may decrease if the patient does not actively use the apps. In 2016, Payal Agarwal et al. [12] investigated the impact of “Bluestar,” an application developed for self-management of diabetes and approved by the Food and Drug Administration, among different clinical sites and health systems. They conducted a pragmatic, multicenter, randomized trial in three recruitment sites. They reported low usage of the app among participants, with a mean number of log-in days of 42.4 (SD 52.1) over 26 weeks, with 46.4% (51/110) of the participants using the app for 10 days or less, and the results showed no difference in HbA1c between the intervention and control groups [12].

One of the strengths of the present study is the use of an AI-driven dietary solution for the record of dietary intake. The image-assisted dietary assessment was shown in previous studies to reduce underreporting of dietary intake compared with traditional methods [13]. The dietary program in this study is expected to be more convenient and effective in that it recognizes all foods by a single capture utilizing the AI solution. Also, for user-friendliness, participants can see their various healthcare data, such as glucose level, body weight, blood pressure, daily activity, and dietary data, on the digital integrated healthcare platform app by connecting Bluetooth-enabled at-home measurement devices including a glucometer, scale, sphygmomanometer, and watch-type pedometer.

A randomized controlled study [14] that aimed to investigate the efficacy of a text message-based diabetes self-management support intervention (SMS4BG) in subjects with diabetes was conducted from 2015 to 2016 in New Zealand. The study showed a significantly greater reduction in HbA1c in the intervention group (mean − 8.85 mmol/mol) than in the control group (− 3.96 mmol/mol) (*p* = 0.007) after 9 months. The result suggests that text messages help diabetes patients with self-management. Furthermore, this current study, which utilizes the digital integrated healthcare platform, will involve health information monitoring and intervention via regular educational text messages from medical staff to provide feedback and encourage patients to continue self-management of diabetes. Thus, the contents of diabetes self-management will not be separated but linked to medical care in the clinic.

Therefore, the results of the current study of the digital integrated healthcare platform with an AI-driven dietary solution and CGMS can yield a positive impact on the self-management of diabetes in patients with type 2 diabetes mellitus.

## Data Availability

Not applicable.

## Abbreviations

AI: Artificial intelligence
Apps: Mobile (smartphone) applications
BMI: Body mass index
CGMS: Continuous glucose monitoring system
CV: Coefficient of variation
DM: Diabetes mellitus
DTSQ: Diabetes treatment satisfaction questionnaire
HDL: High-density lipoprotein
LDL: Low-density lipoprotein
TAR: Time above range
TBR: Time below range
TIR: Time in range
T2DM: Type 2 diabetes mellitus
